### Statistical analysis

This study uses both quantitative and qualitative data analyses. Quantitative data collected from the opinion survey will be analysed using both descriptive and inferential statistical methods to evaluate public attitudes toward heritable human genome editing (HHGE) in South Africa. Descriptive statistics will be used to summarise response frequencies across the 19 HHGE scenarios, offering an overview of levels of support, conditional support, uncertainty, and opposition.

These results will also be disaggregated by key demographic characteristics to provide a demographic profile of the survey sample. To explore the relationships between demographic characteristics and participants’ attitudes toward genome editing, the study will employ chi-square tests for categorical variables and logistic regression models where appropriate. These inferential methods will allow the research team to examine how variables such as education level, population group, and religious affiliation influence support for or opposition to particular genome editing applications.

A key analytical focus of the study is the comparison between private morality (personal decisions regarding one’s own child) and public morality (policy views on what should be legally permitted). The paired responses to these questions will be systematically analysed to assess the extent to which individuals differentiate between personal choice and public regulation. This analysis will also explore whether such divergences are associated with specific demographic factors or interpretations of what constitutes ‘safe and effective’ genome editing.

All statistical analyses will be conducted using GraphPad Prism and/or SPSS, based on the analytical requirements and preferences of the research team. This approach ensures both breadth and depth in interpreting the data, allowing for general trends to be identified alongside more detailed subgroup analyses.

### Qualitative analysis

In addition to quantitative responses, the survey includes several open-ended questions designed to elicit qualitative insights into public attitudes toward HHGE. These include participants’ explanations for selecting ‘yes, but subject to certain conditions’ in response to scenario questions, reflections on the meaning of ‘safe and effective,’ and any general comments provided at the end of the survey. These qualitative data will be analysed thematically to deepen the understanding of how the South African public interprets and reasons about the ethical and social dimensions of genome editing.

Thematic analysis will be conducted using a hybrid approach that combines manual coding with the support of generative artificial intelligence (GenAI) tools. Manual coding will be performed using NVivo software, with the research team developing a coding framework based on an initial review of the data. Simultaneously, GenAI tools – specifically ChatGPT, Grok, and the AI features of NVivo – will be used to conduct parallel analyses. These tools will assist in identifying recurring patterns, emergent themes, and possible interpretive gaps. All GenAI analyses will be guided by the coding framework established by the research team, and their outputs will be treated as audit contributions within an interdisciplinary collaborative model. Final decisions about the inclusion and interpretation of codes and themes will remain with the principal investigator, who will assess the coherence, relevance, and rigour of both human- and AI-generated analyses. This dual-track strategy allows for triangulation of findings, enhances the comprehensiveness of the thematic analysis, and provides a methodological foundation for the satellite study that will compare manual and GenAI-assisted coding. The qualitative analysis is thus not only instrumental in interpreting this study’s findings but also contributes to broader methodological inquiry into the use of AI in empirical bioethics research.

### Reporting and sensitivity to cultural and religious identity

While the survey collects demographic information such as religious affiliation, these data will not be used to characterise or label specific groups. Rather, they serve to contextualise how broader social and cultural factors may shape public reasoning about heritable human genome editing (HHGE). All findings will be reported in aggregate form to reflect general trends in public opinion, without attributing specific positions or values to any religious or cultural community. This approach supports the development of culturally sensitive and inclusive policy insights while avoiding biased or sensationalist interpretations that could reinforce stereotypes or stigmatise particular groups.

### Use of AI tools for thematic analysis

This study contributes to methodological innovation by formally integrating GenAI tools into the process of qualitative data analysis. While traditional manual coding remains central to the thematic interpretation of open-text responses, GenAI tools, specifically ChatGPT, Grok, and NVivo AI, will serve as parallel analytical auditors. This approach is rooted in an interdisciplinary collaborative auditing model [21], in which each GenAI tool is treated as a non-human auditor, contributing analytical suggestions for review and critical comparison by the human research team. The use of AI tools primarily enhances efficiency (speed and scalability when handling large qualitative datasets), consistency (reducing variation among individual coders), and exploratory depth.

The inclusion of multiple GenAI applications acknowledges the variability in how different systems process qualitative data. By comparing outputs across tools, the study enables triangulation and provides a richer understanding of the data than would be possible through manual coding alone. Importantly, this strategy is not intended to replace human judgment but to augment it, thereby supporting consistency, efficiency, and breadth in theme identification, particularly across a large sample of participants. AI tools will be used only as supportive aids in the qualitative analysis, with all outputs critically assessed by the human research team.

To ensure ethical compliance and protect participant confidentiality, all AI-assisted analyses will be conducted on a de-identified dataset. Identifiable information, including names, contact details, or any traceable responses, will be removed prior to processing. Furthermore, privacy settings on the GenAI tools will be configured to prevent data retention or sharing beyond the research team.

To mitigate algorithmic bias and ensure cultural sensitivity, human coders will generate their own codes and use AI only for triangulation. AI-generated interpretations will be reviewed for cultural and linguistic appropriateness, and any problematic outputs will be documented and corrected as part of the audit trail. Discrepancies will be resolved through team deliberation, drawing on the team’s diversity in age, sex and cultural background, and refined analyses may undergo additional peer review to introduce further diverse perspectives. Final coding and interpretation decisions will rest exclusively with the human researchers.

The methodological contribution of this study lies not only in the novel application of AI in qualitative bioethics research but also in its creation of a secondary dataset for a future satellite study. That follow-on project will critically evaluate the epistemological implications, efficiency, and consistency of GenAI-assisted coding in comparison to manual coding. It will be conducted under a separate research protocol and ethical clearance.

## Data management, access, and security

All data collected in this study will be handled with strict attention to confidentiality, data integrity, and secure storage. The study involves two phases of data collection – initial screening and the main opinion survey – each governed by clear procedures for informed consent and access control.

### Informed consent and participation

Participants are required to give written informed consent via online forms at both phases of the study. The first consent form is presented prior to completing the screening questionnaire and outlines the purpose of the research, the voluntary nature of participation, and how personal and survey data will be used. Only those who provide consent may proceed with demographic screening. Participants selected for the opinion survey will be presented with a second online informed consent form before starting the main questionnaire which they will have to complete by writing or ticking the appropriate box. Participants will be informed through the informed consent process that their cell phone numbers will be used solely for issuing compensation and will be permanently deleted once compensation is completed. They will also be informed that their survey responses will not be linked to their email addresses or cell phone numbers and will be informed about how it and where it will be stored securely for research purposes. Participants will have the right to withdraw from the survey at any point before submitting their responses. Participants are informed that compensation will only be issued upon full completion of the opinion survey, and no incentives are offered for the screening phase.

### Fraud prevention and data validation

To ensure the integrity of the dataset, multiple measures will be implemented to prevent fraudulent participation, including responses from non-South Africans and bots:
South African Residency Verification: Participants must provide a valid South African cell phone number, which will be used to distribute compensation.Single Submission Restriction: SurveyMonkey will be configured to allow only one response per unique cell phone number, preventing multiple entries by the same individual.Bot Detection Measures: SurveyMonkey’s CAPTCHA verification and automated spam detection systems will be enabled to prevent bots from submitting responses.

A limitation of the study is that restricting one submission per unique cell phone number cannot fully eliminate the possibility of duplicate participation using multiple devices. However, collecting national identification numbers or similar metrics would not be ethically or legally permissible under South Africa’s Protection of Personal Information Act (POPIA) and could not be independently verified. To mitigate this risk, the survey platform records metadata such as time stamps and response patterns to identify anomalies, and the modest incentive value further reduces motivation for fraudulent participation. While some residual risk remains, these safeguards are considered proportionate and appropriate to the study’s minimal-risk, online design.

### Storage, security and access of data

The email addresses, cell phone numbers, unique participant ID and survey responses will be stored locally on the Principal Investigator and the research assistant’s password-protected notebooks. The data stored locally will be deleted upon completion of the study and publication of the results. Only the finalised datasets, outlined below, will be stored on the university’s Figshare cloud (Yabelana), as per UKZN’s Research Data Management Policy. The data stored on the university’s cloud will be retained for a minimum of 10 years, as per policy, as deleted thereafter.

Access to research data will be carefully managed to protect participant confidentiality. Only the PI and research assistant will have access to the raw data containing the personal details (email addresses and cell phone numbers). Before analysis, identifiable data, such as email addresses or cell phone numbers, will be removed. The dataset, containing only survey responses and demographic information, will be shared securely with the statistician. This will be referred to as the ‘Analysis Dataset’ which will be for internal use, as the qualitative responses might contain indirect identifiers. Only the PI, research assistant, and statistician will have access to the Analysis Dataset, which will be deleted upon completion of the study. Thus, before publication, the research assistant will meticulously check all the qualitative responses for indirect identifiers and redact these, if any are found. The PI will provide a second round of checking. This dataset will be the ‘Publication Dataset’. This approach ensures that personal details (email addresses and cell phone numbers) are handled only for essential administrative purposes, and that all analytical and publication work is conducted using data that is not linked to these details. Only the ‘Publication Dataset’, free of personal identifiers or links to identifying information, will be uploaded to Yabelana Figshare to be retained for a minimum of 10 years, after which it will be deleted. The handling of the data in this way ensures that participants’ responses cannot be linked back to them and may give them greater confidence to participate in the study.

In terms of the qualitative responses specifically, all such data will undergo a rigorous anonymisation process prior to analysis. In addition to the two-phase consent procedure and existing confidentiality safeguards, we will implement a two-stage anonymisation protocol. First, a member of the research team will review raw text to remove or replace any direct identifiers, including names, organisations, workplaces, and specific geographic references. A second team member will then cross-check the anonymised transcripts to identify and generalise any indirect identifiers, such as unique personal circumstances or rare demographic combinations.

Demographic variables will be used only in aggregate, and no participant will be identifiable through demographic clusters. Any quotations used in reporting will be paraphrased or further generalised where there is a risk of deductive disclosure. In addition, anonymised excerpts will be reviewed collectively during team coding discussions, enabling multiple perspectives to detect residual identifying information. These steps ensure that all qualitative data are fully anonymised prior to analysis and that the risk of unintended identification is minimised.

## Discussion

The prospective study based on this protocol offers a timely and necessary intervention into the emerging field of public engagement with HHGE, particularly within underrepresented contexts such as South Africa. By capturing the spontaneous, non-deliberative views of a demographically representative population sample, it responds to growing calls for more inclusive and locally grounded data on public attitudes toward genomic technologies.

For practice, the prospective study will provide empirical insights into how South Africans interpret core ethical concepts such as safety, effectiveness, and permissibility in the context of HHGE. These findings can assist clinicians, genetic counsellors, and science communicators in better understanding how laypeople perceive risk, choice, and therapeutic intention, enabling more responsive engagement and communication strategies in clinical and community settings.

For policy, the study will offer robust public opinion data that can inform governance frameworks for genome editing in South Africa. Unlike deliberative studies that rely on informed participants, this survey captures widespread public sentiment, including moral and cultural intuitions that may otherwise remain invisible in policymaking processes. The dual framing of private and public morality further enriches the data, offering insights into how individuals differentiate between personal autonomy and societal regulation. These perspectives are essential for ethical policy development, particularly in democratic societies seeking legitimacy through public consultation.

For scholarship, the study contributes to global literature by expanding the geographic and methodological scope of public opinion research on HHGE. It introduces an innovative comparative design that links deliberative and spontaneous viewpoints, and it pioneers the integration of generative AI tools in qualitative data analysis. This methodological contribution lays the groundwork for future research into the epistemological, ethical, and practical implications of AI-assisted qualitative methods in empirical bioethics.

Through its design and scope, the study supports a more inclusive, context-sensitive, and methodologically plural understanding of how emerging biotechnologies are received by the public, which is an essential step in fostering ethically sound and socially legitimate science policy.

## Limitations

While the study is designed to maximise representativeness and rigour, several limitations must be acknowledged. There are three limitations that can be identified from the outset of the study: limitations in Facebook recruitment; the cross-sectional versus longitudinal nature of the study; and the use of GenAI in analyses.

First, the online nature of recruitment may exclude individuals without reliable internet access, particularly in rural or economically disadvantaged areas. This constitutes a limitation of the sampling approach. No supplementary recruitment strategies will be implemented beyond the online platform, and this limitation is acknowledged explicitly. Facebook advertising was selected as the primary recruitment method because it offers a cost-effective way to reach a national audience within the study’s resource constraints. Complementary recruitment strategies, particularly in rural areas, are not feasible due to the financial and logistical demands of travel, translation and gatekeeper permissions. We acknowledge that this may lead to under-representation of some groups and note this as a limitation and an avenue for future research. Nevertheless, recent national data suggest that as of January 2024, 66% of the population within the age group of 16 to 65 likely use Facebook [10]. While this figure may not capture all usage patterns, it suggests that Facebook provides extensive coverage of the general adult population, including a substantial proportion of users from diverse socioeconomic backgrounds. Given that the aim of this study is to explore public attitudes toward HHGE rather than to produce nationally representative estimates, recruitment through Facebook remains a reasonable and pragmatic approach.

Second, as a cross-sectional survey, the study captures views at a single point in time and does not account for how public attitudes may evolve through exposure to new information or public debate. The absence of a deliberative component means that changes in opinion arising from education, reflection, or dialogue are not measured within this study.

Third, while the use of generative AI tools enhances the scale and consistency of qualitative analysis, these tools may produce overly broad, generic themes, or introduce bias, without human oversight. As such, the integration of AI is exploratory and will be accompanied by critical human review. All AI-assisted coding outputs will be cross-checked against a subset of data manually coded by members of the research team to ensure consistency and accuracy. Discrepancies between human and AI coding will be discussed, and final thematic categories will be confirmed through consensus among the research team. Recognising that AI models may reproduce or amplify bias present in their training data, all outputs will be reviewed critically by human coders for contextual and cultural appropriateness, especially given the sensitivity of the South African setting. AI-generated outputs will only be accepted once these are verified by a member of the research team.

Despite these limitations, the study offers a valuable and novel dataset that will inform future research, engagement efforts, and policymaking on HHGE in South Africa and comparable contexts.

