## Research objectives

The study is guided by the following research objectives:To determine the level of public support for potential HHGE applications in the future aimed at specific health scenarios, including:
Editing to correct genetic errors to prevent categories of genetic conditions, ranging in the severity of their health-related symptoms or complications and/or sociocultural implications in the South African setting;Editing to confer immunity against categories of infectious diseases which range in the severity of their health-related symptoms or complications, with a sub-focus on editing to prepare a population for hypothetical pandemic scenarios;Editing to influence non-health-related traits, also referred to as enhancement.To examine demographic variations in public opinion, by analysing responses according to population group, age, sex, and education level.To compare:
Spontaneous public opinion captured in this study with deliberative public views reported by [name] et al. [9].Private moral choices (what individuals would choose for their own child) with public moral views (what individuals think the law should allow for society at large).To assess public perspectives on the temporal focus of science policy, specifically whether it should focus solely on what is currently safe and effective or also consider future scientific developments that may become safe and effective.To identify public interpretations of what constitutes ‘safe and effective’ HHGE and examine how these interpretations influence participants’ support for various applications of genome editing.To contribute to the global literature on HHGE, by:
Identifying alignments or divergences between South African public opinion and trends observed in high-income countries.Exploring the influence of local health challenges and socio-cultural contexts on attitudes toward HHGE.

By achieving these objectives, the study will provide robust empirical evidence to inform policy, ethical debates, and governance frameworks on genome editing in South Africa and comparable settings.

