### Study design

This study employs a cross-sectional survey design to measure spontaneous public opinion on various potential applications of HHGE among adult residents of South Africa. The survey is conducted online using SurveyMonkey and is structured around 19 scenarios derived from those used in the deliberative public engagement study by [name] et al. [9]. Of these scenarios, 15 correspond to [name] et al.’s [9] previous study, and there are five new scenarios that have been added or amended. Four of these scenarios relate to pandemic preparedness, a relevant topic given the recent COVID-19 pandemic. Furthermore, an additional new scenario, involving the creation of novel eye colours, has been included to explore public perceptions of genetic modifications beyond species-typical traits. These are explained further under the sub-section for ‘Survey instrument’. The inclusion of questions on both private morality (personal choice) and public morality (policy preference) provides a dual-lens analysis of ethical reasoning. Furthermore, participants will be asked to interpret the phrase ‘safe and effective’ to examine how their conceptual understanding shapes their views on the permissibility of HHGE applications.

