### Survey instrument

The survey instrument comprises two components: a demographic screening questionnaire and the main opinion survey assessing public views on HHGE. Optional open-text fields are included throughout to capture qualitative insights. Only respondents who complete the screening questionnaire and provide informed consent via the online form are considered for inclusion in the opinion survey. Collectively, the instrument is designed to elicit structured, comparative data while allowing for nuanced interpretation of underlying values through optional free-text responses.

The opinion survey (see Supplementary Materials) is organised into four sections:
**Interpretation of ‘safe and effective’** – examines how participants conceptualise safety in the context of HHGE by selecting among different definitions and, if desired, elaborating in an open-text response. To account for variability in how participants interpret ‘safe’ and ‘effective,’ the survey provides three predefined interpretive options for each term, based on widely accepted scientific and ethical understandings. Participants may also select ‘Other’ and provide their own explanation. These free-text responses will be reviewed to determine whether they align with the predefined categories or represent distinct interpretations. Patterns in ‘Other’ responses will be analysed to assess how public understandings converge or diverge from one another and from established scientific and health ethics definitions of safety and efficacy and public views on these matters [3].**Policy scenarios** – presents a range of possible HHGE applications, covering therapeutic, preventive, and enhancement purposes. Each scenario includes two decision contexts: a *private* decision (for one’s own hypothetical child) and a *public* decision (policy preference for society). This structure enables comparison between individual and collective moral reasoning.**General comments** – provides space for participants to express broader reflections on HHGE.**Media engagement** – records whether participants viewed the optional pre-survey educational videos or other media content related to genome editing.

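### Objective 5 and the design section state a causal aim (interpretations of safe and effective influence or shape support) that a one-survey, self-chosen definition can show only as an association

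*Protocol article*

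**What the plan says.** Objective 5, under Research objectives, is to identify how the public interprets safe and effective and to "examine how these interpretations influence participants’ support for various applications of genome editing". The Study design section says participants are asked for their interpretation "to examine how their conceptual understanding shapes their views on the permissibility of HHGE applications".

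The same section describes the design: "This study employs a cross-sectional survey design to measure spontaneous public opinion on various potential applications of HHGE". Under Survey instrument, the first section of the opinion survey "examines how participants conceptualise safety in the context of HHGE by selecting among different definitions", and "the survey provides three predefined interpretive options for each term, based on widely accepted scientific and ethical understandings", with a free-text *Other* choice. The policy scenarios are the second section of the same survey.

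The Statistical analysis section uses associational language for interpretations, in one place: the analysis of paired private and public answers will "explore whether such divergences are associated with specific demographic factors or interpretations" of safe and effective. That sentence concerns private-public divergence, not support.

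The second limitation reads: "as a cross-sectional survey, the study captures views at a single point in time and does not account for how public attitudes may evolve". It then adds that opinion change through education, reflection or dialogue is not measured. Neither it nor the other two limitations (Facebook recruitment and generative AI) mentions the direction of the relation or shared causes.

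**The concern.** *Influence* and *shapes* name a direction: the definition comes first and support follows. For that to be learned from data, the definition would have to be assigned, varied, or at least fixed before the attitude formed. Here the respondent picks it.

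Two other explanations yield the same table. Someone already opposed to heritable editing may pick the definition that fits that view (reverse direction). Or a third factor, such as religion, education or a general attitude to the technology, may drive both answers (common cause). The Statistical analysis section itself expects education, population group and religion to bear on support, so if any of these also affects the chosen definition it is a common cause.

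At stake is what the study may conclude. The Discussion says the findings on how people understand safety and effectiveness should help science communicators and inform governance. If the association is read as an effect, the natural inference is that clarifying what safe means would move public support. The design cannot bear that inference.

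**Working it through.** **The plan's own figure.** The Sample size justification gives 385 for ±5% at 95% confidence. n = z²p(1−p)/d² = 1.96² × 0.25 / 0.05² = 384.15, rounded up to 385. It reproduces. At n = 400 the margin is ±4.9 points. This figure concerns a single proportion and is unaffected by the present point.

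**Inputs for the check.** From the documents: n = 400, and a self-chosen definition recorded in the same survey as the outcome. Not in the documents, and therefore assumed: the level of support, the share choosing each definition, and the strength of any link. For illustration the definitions are collapsed to one restrictive choice versus the rest. The article does not say its options are ordered by strictness. In every case below the definition has **no effect** on support. Chances of significance use the two-sample normal approximation at two-sided 5%.

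**A. Reverse direction.** Support is 50%. Let o and s be the proportions of opponents and supporters who pick the restrictive definition. Then

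P(support | restrictive) = 0.5s / (0.5s + 0.5o)

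P(support | other) = 0.5(1−s) / [0.5(1−s) + 0.5(1−o)]

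For o = 50%, s = 25%: 0.125/0.375 = 0.333 and 0.375/0.625 = 0.600.

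| o v s | Support, restrictive v other | Gap | Chance of p < 0.05 |
|---|---|---|---|
| 50% v 25% | 33% v 60% | 27 points | about 100% |
| 45% v 30% | 40% v 56% | 16 points | 88% |
| 45% v 35% | 44% v 54% | 10 points | 54% |
| 40% v 35% | 47% v 52% | 5 points | 18% |

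**B. Measured common cause.** A group making up 40% of the sample supports editing at 30% (others 60%) and picks the restrictive definition at 60% (others 30%).

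- Restrictive share: 0.4 × 0.6 + 0.6 × 0.3 = 0.42.
- Group share among restrictive choosers: 0.24/0.42 = 0.571. Their support: 0.571 × 0.30 + 0.429 × 0.60 = 0.429.
- Group share among the rest: 0.16/0.58 = 0.276. Their support: 0.276 × 0.30 + 0.724 × 0.60 = 0.517.
- Crude gap: 9 points, with a 42% chance of significance. Within each group the gap is zero, so adjustment for the group removes it. That follows only because the sole common cause in this example is measured.

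**C. Unmeasured shared attitude.** A latent attitude loads equally (λ) on the tendency to choose a permissive definition and on support, so the two latent scales correlate at λ². Support is 50% and 33% choose the permissive definition. Support among permissive choosers is Φ₂(Φ⁻¹(0.33), 0; λ²)/0.33.

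| λ | Gap | Odds ratio | Chance of p < 0.05 |
|---|---|---|---|
| 0.2 | 2.6 points | 1.11 | 0.07 |
| 0.3 | 5.9 points | 1.27 | 0.20 |
| 0.4 | 10.5 points | 1.52 | 0.51 |
| 0.5 | 16.5 points | 1.95 | 0.88 |
| 0.6 | 24 points | 2.68 | >0.99 |
| 0.7 | 33 points | 4.05 | about 1 |

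Varying the permissive share from 20% to 50% at λ = 0.5 gives odds ratios of 1.9 to 2.1 and chances of 0.81 to 0.90.

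**Reading.** An association with no effect behind it can be too small to notice or very large. Its size depends wholly on inputs that nobody has yet.

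**The case against.** The best case for the plan is that this is loose wording and no planned analysis is wrong. The Statistical analysis section also uses *influence* for demographic variables, directly after describing the task as exploring relationships, so the verb may be the article's ordinary word for a regression relation. Both disputed sentences say *examine*; neither promises an effect. The definition is asked before the scenarios. Free text on meaning and on conditions will be analysed thematically, so Objective 5 does not rest on a cross-table alone. Covariate choice is properly left to an analysis plan that is not shown.

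Much of this limits the point without removing it. The associational sentence covers private-public divergence, so it does not correct the wording for support, the outcome of Objective 5. Question order does not fix direction when the attitude may precede the survey. Free text shows how people account for their views, not whether the definition caused them. The absence of a covariate list is rightly not a fault.

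Some stronger readings should be resisted:

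- That a large spurious association is to be expected. The documents give no input for this, and the assumed range starts near zero.
- That both answers are given in one sitting. Participants have two weeks; only the shared questionnaire is documented.
- That opponents will take a strictest option. No ordering of the options is stated.
- That the limitation on cross-sectional design is false. It is true as far as it goes; the fault lies in the objective and design wording.
- That the authors will report an effect. No sentence says so; the wording only leaves room for it.

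**Conclusion.** The point stands as one of wording and interpretation. Objective 5 and the Study design section state a causal aim that this survey cannot meet, and the Limitations section does not say so. An unseen analysis plan could not cure this, because no model makes a self-chosen definition identify an effect without further assumptions.

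The size is conditional. With 400 respondents and a definition that does nothing, the gap in support ranges from a few points to more than 25 points. Significance becomes about as likely as not near a 10-point gap. These figures rest on assumed support of about 50% (48% overall in example B), a two-way split of the definitions and assumed strengths of association. They show what can happen, not what will.

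**What to change.** 1. In Objective 5 and in the Study design section, replace the causal verbs with wording that interpretations *are associated with* support or views, and do not report the result as an effect of the definition.
2. Extend the second limitation: existing support or opposition may drive the chosen definition as well as the reverse, and shared causes cannot be separated in this design.
3. As a secondary step, where interpretation is related to support, report the logistic regression already named in the plan, adjusted for the demographics collected at screening (age, sex, population group, education, religious affiliation) as far as 400 respondents allow. State that this handles measured common causes only, not reverse direction or an unmeasured prior attitude.

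The first two steps cost a few sentences and a weaker claim for Objective 5. The third needs no new data but may meet sparse cells: several multi-category covariates and up to four choices per term, across 19 scenarios with two lenses (38 outcomes), some of which may draw little support. If a causal answer is wanted, the definition shown to respondents would have to be randomised, which is a different study.
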